### Study Design

A three-blind, two-arm, cohort randomized controlled trial will be conducted to evaluate the effects of IERMS-based physical activity on health performance in frail older adults (Registration number: ChiCTR2100052286)^1^. A total of 120 participants will be recruited according to the screening criteria from six community health service centers in Changchun, China, and the participants will be randomly divided into two groups. Participants in the first group will receive a 12-week IERMS-based intervention, and participants in the second group will receive a 12-week conventional care. Then, there will be a 12-week follow-up. Data will be collected at baseline, 12 and 24 weeks. The study design is shown in Figure 1. After the intervention, the same guidance will be given to the second group to ensure that more older adults benefit.

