#### Randomization and Blinding

From each center, 20 participants will be recruited and stratified by gender and age; then, they will be randomly assigned to the first or second group in a 1:1 ratio through a computer-generated randomized list. This task will be performed independently by individuals not involved in the research process. All researchers will be divided into two teams: one team will be responsible for the guidance of group 1, and the other team conduct routine education, they will be ignorant of each other’s content. Throughout the intervention, neither the participants nor the researchers conducting the intervention or the data collection will be aware of the grouping. The study designer and the staff responsible for allocation concealment and data processing will be not permitted to participate in the whole intervention.

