### Intervention

#### Training Based on Intelligent Exercise Rehabilitation Management System

At baseline, all participants will undergo physical function, physical activity, psychology, and cognition assessments. These assessments will be repeated at 12 and 24 weeks. Participants in the first group will receive a pair of smart insoles and a patient-side APP installed on their phone and will learn all the functions of the system. According to the participants’ physical activity level at baseline, professional rehabilitation therapists will select the activity plan from the default scheme (Table 1); upload it to the cloud, which is the management data layer; and send the plan for the next week according to the participants’ weekly completion. If the activity goal of the week is not reached, the plan of the week will be continued. Once the current week’s activities are completed, the plan for the next phase will be carried out. Participants will choose the type of physical activity (Table 2) in the APP according to their preferences and choose the activity day of the week and the training time of each activity according to the target activity days. The system will automatically generate the particular week’s schedule according to participants’ choices and remind them at the time set by participants. At the end of each activity, participants will upload the daily completion of the activity and fill in the specific activity time for unfinished projects. They will have access to view the week’s activity plan at any time and generate the week’s activity schedule every Monday. During the workout, participants will be asked to wear smart insoles that monitor dynamic changes in gait parameters and synchronize them to the cloud in real time. In addition, patients will communicate with professionals through a short messaging service built into the APP and receive feedback within 24 h. The APP interface is shown in Figure 2. Before the start of each training, the user will receive a reminder as follows:

**TABLE 1 T1:** Weekly training schedule.

Current PA (min)	Target PA (min/w)	Mon.	Tue.	Wed.	Thur.	Fri.	Sat.	Sun.
0–30	≥30	Upload last week’s completion Make plans for this week	3 days,1 time/day, 10 min/time					
30–60	≥60		4 days,1time/d					
			1 time:10 min, 2–3 time:15 min, 4 time:20 min					
60–90	≥90		4 days, 1 time/day					
			1–2 time: 20 min, 3–4 time: 25 min					
90–120	≥120		5 days, 1 time/day, 25 min/time					

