### Quality Control

Our research group has established a team of experienced clinical nurses and rehabilitation therapists at a rehabilitation center in Changchun, China. Experienced clinical nurses and researchers from the team will be responsible for recruiting participants. Participants meeting the inclusion criteria will be screened, they will be informed of the study details by the investigator, and if they agree to participate, they will be asked to sign a consent form. If there is a complex clinical problem, our researchers, nursing specialists, and rehabilitation therapists will work together to find a solution.

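### Participants and intervention staff are said to be unaware of grouping, which the trial's own procedures rule out; the three-blind label should be dropped and blinding claimed only for outcome data collectors

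*Protocol article*

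**What the plan says.** The Abstract (Design) and the Study Design section both use the three-blind label; the latter reads "A three-blind, two-arm, cohort randomized controlled trial will be conducted". Randomization and Blinding spells the label out for the intervention period: "neither the participants nor the researchers conducting the intervention or the data collection will be aware of the grouping".

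The sentence before that claim organises the staff by arm: "one team will be responsible for the guidance of group 1, and the other team conduct routine education". It adds that neither team knows what the other delivers. The section closes by keeping the study designer, and the staff who handle allocation concealment and data processing, out of the intervention.

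The section on training with the system describes what group 1 gets: "Participants in the first group will receive a pair of smart insoles and a patient-side APP installed on their phone". It also describes what staff do for that group: "professional rehabilitation therapists will select the activity plan from the default scheme". They then send each following week's plan according to how much of the last one was completed. For the control arm, Study Design says "participants in the second group will receive a 12-week conventional care". Routine Care describes this as health education plus a monthly telephone call, given to everyone. Under Quality Control, eligible people are told about the trial before consenting: "they will be informed of the study details by the investigator".

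**The concern.** The article does not leave blinding open. It asserts it for participants, for those who deliver the intervention and for those who collect data. The intervention is a visible device-and-app programme compared with usual care, so the first two claims conflict with the procedures described elsewhere in the article.

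The label would carry into the trial report. A reader who believes that participants did not know their arm will give the self-reported outcomes more credit than they deserve. These are IPAQ activity, PHQ-9, GAD-7, PSQI, the Fried fatigue question and adverse events. IPAQ is the most exposed: group 1 is guided each week towards targets in activity minutes and is then asked to report activity. The primary outcome, TUG, is a timed performance test and less exposed, but the behaviour of participant and tester can still affect it. The limitations in the Discussion concede error in self-uploaded logs and in self-reported activity. They do not mention that participants know their arm.

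**Working it through.** No figure in the plan bears on this point, so the check sets the blinding claim for each party beside the procedures.

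1. **Participants.** Claim: unaware of grouping. Procedures: group 1 has an app on the phone, insoles to wear during training, a weekly plan, reminders, daily uploads and messaging with professionals. Group 2 has education and a monthly call, which group 1 also has. No sham app, sham device or matched programme is described. A participant can see whether they have the programme. After the intervention group 2 is offered the same guidance, which only makes sense if they did not have it before. Result: the claim cannot hold.

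2. **Researchers conducting the intervention.** Claim: unaware of grouping. Procedures: "one team will be responsible for the guidance of group 1", and therapists choose, upload and update individual plans for that group. Someone assigned to guide group 1 knows that the people they guide are in group 1. Result: the claim cannot hold, and it conflicts with the sentence directly before it.

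3. **Data collectors.** Claim: unaware of grouping. Procedures: the same section divides all researchers into the two arm-specific teams and names no separate group of testers. It nevertheless names data collection as a function distinct from conducting the intervention. Result: the claim is feasible and not contradicted, but the article gives no mechanism for it. The sentence also covers only the intervention period and so does not clearly reach the 24-week assessment.

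4. **Data-processing staff.** Claim: they take no part in the intervention. That is separation from delivery. The article does not say that they work without knowledge of group. Result: analyst blinding is neither stated nor excluded.

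Count: of the 3 parties in the blinding sentence, 2 cannot be blind and 1 can.

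Outcomes that rest on the participant's own report: IPAQ, PHQ-9, GAD-7, PSQI and the Fried fatigue item (5 measures), plus adverse events including falls and admissions.

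**The case against.** The best defence is that the authors meant concealment of content: each team is kept from knowing what the other delivers, and participants may know little about the other arm. It is also true that the article does not say how much the consent discussion reveals about the two arms. This explains how the sentence may have come about, but it does not rescue it. Not knowing the other arm's content is different from not knowing one's own arm, and the article claims the latter. The conflict for intervention staff does not depend on consent at all.

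A second defence is that the primary outcome is timed, gait comes from the device, and the self-reported scales are secondary or safety measures. That stands, and it limits the damage. TUG is described as walking at a regular speed, and the article does not say that it is hand-timed, so no strong claim about its susceptibility should be built on the text.

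Two stronger readings are tempting. A reader might infer, from the division of all researchers into two teams, that the people who time the TUG are the people who deliver the programme. The document does not support that: it states that data collectors are unaware of grouping, and staffing detail may sit in the full protocol. A reader might also conclude that the trial is really assessor- and analyst-blinded. The analyst half of that label has no support in the text. Nor do insoles worn at a test visit reveal the arm in themselves, because the gait assessment requires them and Table 3 schedules it without restriction to one arm.

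**Conclusion.** The point holds for participants and for researchers conducting the intervention. The article claims a blinding property that its own procedures exclude, so the three-blind label is wrong as written. An open comparison of an app-based programme with usual care is not a bad design; the description is what fails.

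The size of the resulting bias cannot be computed from the document. What can be stated is the reach: 2 of 3 claimed blinding levels, 5 self-reported secondary measures and adverse events. The primary TUG is affected to the extent that participant or tester behaviour changes a timed performance test, which is a judgement and not a figure in the plan. The conclusion assumes that group 2 receives no sham device or app, and none is described. Blinding of data collectors remains possible and is not disputed.

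**What to change.** - Remove the three-blind label from the Abstract and Study Design.
- In Randomization and Blinding, state that participants and intervention staff are not blinded, and keep the blinding claim for outcome data collectors only.
- Support that claim: specify that those who carry out the TUG, gait and Fried tests at 0, 12 and 24 weeks have neither delivery role for the participants they test. Existing staff can do this.
- Use the same insole procedure at testing in both arms.
- Claim analyst blinding only if data-processing staff will in fact work without knowledge of group.
- Add participants' awareness of their arm to the limitations in the Discussion.
- State that IPAQ, PHQ-9, GAD-7, PSQI, Fried fatigue and adverse events will be interpreted as open-label.

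The cost is wording and the assignment of existing staff to test visits. Sample size, outcomes and the analysis model are unchanged. The downside is that the stated level of blinding becomes less favourable.

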### Intervention

#### Training Based on Intelligent Exercise Rehabilitation Management System

At baseline, all participants will undergo physical function, physical activity, psychology, and cognition assessments. These assessments will be repeated at 12 and 24 weeks. Participants in the first group will receive a pair of smart insoles and a patient-side APP installed on their phone and will learn all the functions of the system. According to the participants’ physical activity level at baseline, professional rehabilitation therapists will select the activity plan from the default scheme (Table 1); upload it to the cloud, which is the management data layer; and send the plan for the next week according to the participants’ weekly completion. If the activity goal of the week is not reached, the plan of the week will be continued. Once the current week’s activities are completed, the plan for the next phase will be carried out. Participants will choose the type of physical activity (Table 2) in the APP according to their preferences and choose the activity day of the week and the training time of each activity according to the target activity days. The system will automatically generate the particular week’s schedule according to participants’ choices and remind them at the time set by participants. At the end of each activity, participants will upload the daily completion of the activity and fill in the specific activity time for unfinished projects. They will have access to view the week’s activity plan at any time and generate the week’s activity schedule every Monday. During the workout, participants will be asked to wear smart insoles that monitor dynamic changes in gait parameters and synchronize them to the cloud in real time. In addition, patients will communicate with professionals through a short messaging service built into the APP and receive feedback within 24 h. The APP interface is shown in Figure 2. Before the start of each training, the user will receive a reminder as follows:

**TABLE 1 T1:** Weekly training schedule.

Current PA (min)	Target PA (min/w)	Mon.	Tue.	Wed.	Thur.	Fri.	Sat.	Sun.
0–30	≥30	Upload last week’s completion Make plans for this week	3 days,1 time/day, 10 min/time					
30–60	≥60		4 days,1time/d					
			1 time:10 min, 2–3 time:15 min, 4 time:20 min					
60–90	≥90		4 days, 1 time/day					
			1–2 time: 20 min, 3–4 time: 25 min					
90–120	≥120		5 days, 1 time/day, 25 min/time					
120–150	≥150		5 days, 1 time/day, 30 min/time					

**TABLE 2 T2:** List of physical activities available to participants.

01. Walking quickly	11. Badminton	21. Plank support
02. Running	12. Table tennis	22. Pushups
03. Tai Ji	13. Volleyball	23. Sit-ups
04. Skipping rope (≥100 time/min)	14. Football	24. Pull-ups
05. By bike (outdoor > 8 km/h)	15. Basketball	25. Lunge
06. By bike (gym > 8 km/h)	16. Tennis	26. Jumping jacks
07. Upstairs	17. Swimming	27. Squat
08. Downstairs	18. Martial arts	28. Pilates
09. Wash the car	19. Skating	29. Aerobic dance
10. Do housework	20. Skiing	30. Yoga

**FIGURE 2 F2:**
[figure not shown]
Prototype of the app user interface.

Before activity: Warm-up ≥ 5 min.

After activity: stretch ≥ 5 min.

The time of each successive activity: ≥ 10 min.

The interval between two activities: ≤ 3 days.

Please don’t be nervous if you feel strenuous or the heart rate significantly accelerated in the process of activity, this is a normal phenomenon. But if you feel unwell, please seek medical advice immediately.

#### Routine Care

All participants will receive a routine nursing care. The rehabilitation therapist will provide health education on frailty and physical activity: manifestation, risk, prevention, screening, and treatment of frailty; benefits of moderate physical activity; and introduction of common forms are listed in Table 2. A registered nurse will conduct a telephonic follow-up for all participants once in a month.

### Outcome Measures

In this study, the primary outcome will be the objective changes in physical function. At the same time, other measuring tools will be used to evaluate the multidimensional efficacy of the intervention, and a less number of participants will be selected for semi-structured interviews to gain an in-depth understanding.

#### Primary Outcome

##### Physical Function

The physical function will be evaluated by the Timed Up & Go (TUG) test (Mathias et al., 1986), which assesses the basic mobility skill as well as strength, balance, and mobility. In this test, the subjects will stand up from a standard chair (the chair with a height of 46 cm and arms with a height of 65 cm), wear comfortable shoes, walk at a regular speed of 3 m, turn around, walk back to the chair, and sit down in the chair, and then will stop the timer. According to the test results, ≤ 10 s will be considered completely independent, 10–19 s will be considered to be independent, between 20 and 29 s will be considered a “gray area,” and more than 30 s will be considered to be completely dependent. Its reliability and effectiveness have been verified in various populations (Chan et al., 2017; Yuksel et al., 2017).

#### Secondary Outcomes

##### Gait Parameters

Gait parameters include walking speed, symmetry, and variability. Participants will wear smart insoles and walk more than 25 m on barrier-free horizontal roads for at least 2 min at their self-selected comfortable pace. The walking process will include four parts, namely, acceleration, deceleration, uniform speed, and turning. The system will complete the gait analysis during this period. Walking speed (m/s) is defined as the walking distance per unit time, and when it is less than 0.6 (Zaccardi et al., 2019), there will be a higher risk of falls. Gait variability is defined as the variable coefficient of all the step-by-step cycles and is used to evaluate the variation of temporal parameters. The normal range is 2–3%, and higher values are regarded as unstable. Gait symmetry is defined as the ratio of the swinging time of biped in the air and is usually around 1.02% for healthy adults.

##### Frail Score

The frailty phenotype represents the most known operational definitions of frailty in older persons (Fried et al., 2001). According to the Fried phenotype: 0 = health; 1–2 = pre-frailty; and ≥ 3 = frailty. Walking speed, grip strength, weight, physical activity, and self-reported fatigue will be measured by the methods as shown in Table 3. One point will be recorded when any items reach the cutoff value.

**TABLE 3 T3:** Indicators collected and assessment tools at each time point.

Test	Content				Time point				
					Screen	Baseline		12 w	24 w
FRAIL	The simple “FRAIL” questionnaire screening tool				√					
	Fatigue	Are you fatigued?							
	Resistance	Cannot walk up one flight of stairs?							
	Aerobic	Cannot walk one block (500 m)?							
	Illnesses	Do you have more than 5 illnesses?							
	Loss of weight	Have you lost more than 5% of your weight in the last 6 months?							
	Scoring: 3 or greater = frail; 1 or 2 = prefrail								
Demographic	Standardized questionnaire assessing age, gender, education level, residential status, falls history, medical history and so on.					√		√	√
Gait	Gait parameters generated by the device					√		√	√
TUG	Timed up and go test					√		√	√
Fried	Scoring: 3 or greater = frail; 1 or 2 = prefrail; 0 = health					√		√	√
	Walking speed	Slow gait: < 1.0 m/s							
	Grip strength	Measure three times and take the optimum							
		Low grip strength as follows:							

		**Males**		**Females**					
		**BMI**	**Grip strength (kg)**	**BMI**	**Grip strength (kg)**				

		≤24	≤29	≤23	≤17				
		24.1–28	≤30	23.1–26	≤17.3				
		≥28	≤32	26.1–29	≤18				
	Weight loss	Methods: measure three times and take the average, after urination in the morning							
		Weight loss: an unintentional weight loss ≥ 10 kg/10% over the previous year or an average monthly loss ≥ 1 kg/1%							
	Insufficient physical activity	≤150 min of light to moderate physical activity per week, or ≤ 75 min of vigorous physical activity per week, or the total level of physical activity did not achieve the same amount of expenditure							
	Fatigue	Asking question “Do you feel too weak to do what you want to do in the last month?” If the participants answered “yes,” they will be considered fatigued							
MVPA	Short International Physical Activity Questionnaire						√	√	√
	High	Meet any one of the following 2 standards							
		Vigorous activity ≥ 3 days and total level ≥ 1,500 MET							
		The total physical activity ≥ 7 days and 3,000 MET-min/w							
	Sufficient	Meet any one of the following 3 standards							
		Vigorous activity ≥ 20 min per day and total ≥ 3 days							
		Moderate and/or walking ≥ 30 min per day and total ≥ 5 days							
		The total physical activity ≥ 5 days and 600 MET-min/w							
	Low	Meet any one of the following 2 standards							
		No activity was reported							
		Some activities reported, but not meet the criterion of the above sufficient and high							
PHQ-9	Patients Health Questionnaire 9-item						√	√	√
GAD-7	Generalized Anxiety Disorder 7-item						√	√	√
MMSE	Mini-Mental State Examination						√	√	√
PSQI	Pittsburgh Sleep Quality Index						√	√	√

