##### Other Secondary Outcomes

The difference between the percentage of walking speed < 0.6m/s, gait variability > 3%, frailty score ≥ 3, and low physical activity will also be compared.

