However, this study still has certain limitations. First, the sample size is small and the population is limited to five communities in Changchun, so the results may not be fully promoted. Second, the training log is uploaded by the participants themselves, and there is still a certain problem with its authenticity. Finally, the body activity amount is calculated by the self-reported exercise form and metabolic equivalent, so there is a certain deviation in the calculation of exercise amount.

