## Conclusion and Implications

In general, we designed a personalized remotely supervised physical activity program and expected to add effect by increasing the participation. Based on the evidence, we are convinced that this intervention program will be able to delay or reverse the progress of frailty. If the intervention produces a significant positive effect, the findings will potentially provide valuable evidence and serve as convenient and feasible strategies for primary healthcare to promote healthy aging.

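### The five-item frailty score gives a point for low weekly activity, the behaviour that group 1 is assigned to change, so part of any fall in the score may be uptake of the programme

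*Protocol article*

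**What the plan says.** Frail Score defines a secondary outcome on the Fried phenotype. The components are listed thus: "Walking speed, grip strength, weight, physical activity, and self-reported fatigue will be measured by the methods as shown in Table 3". Each carries equal weight: "One point will be recorded when any items reach the cutoff value". The classes are fixed: "According to the Fried phenotype: 0 = health; 1–2 = pre-frailty; and ≥ 3 = frailty". Table 3 gives the cutoff for the activity item as "≤150 min of light to moderate physical activity per week, or ≤ 75 min of vigorous physical activity per week", or an equivalent total not reached. In Table 3 the FRAIL questionnaire is marked at screening only, so the Fried score is the only frailty measure repeated at 12 and 24 weeks.

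The intervention section and Table 1 assign group 1 weekly minutes of activity, starting from the participant's own level and rising by steps. The last step is "5 days, 1 time/day, 30 min/time", with a target of at least 150 min per week. Group 2 receives routine care (education and a monthly call), which group 1 also receives.

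Other Secondary Outcomes adds comparisons of percentages, among them "frailty score ≥ 3, and low physical activity will also be compared". Statistical Analysis compares changes from baseline by GEE. The Discussion concedes that "the body activity amount is calculated by the self-reported exercise form and metabolic equivalent", and the Conclusion states that "we are convinced that this intervention program will be able to delay or reverse the progress of frailty".

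**The concern.** In an observational cohort, low activity can serve as a marker of frailty. Here activity is the randomised treatment, so at the end of the intervention the item records, at least in part, whether the treatment was taken up. Four items (gait speed, grip, weight loss, fatigue) can show a response to the programme. The fifth can change because the programme was followed, or was reported as followed.

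What is at stake is interpretation. A between-group difference in the total score, or in the share scoring 3 or more, could be read as frailty delayed or reversed when some or all of it is the activity point. The article does not mention this overlap among its limitations.

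**Working it through.** **1. Assigned activity against the outcome cutoff.** The article gives no expected value for the frailty score, so the only figures to reproduce are the weekly totals in Table 1:
- 3 × 10 = 30 min (target ≥30)
- 10 + 15 + 15 + 20 = 60 min (target ≥60)
- 20 + 20 + 25 + 25 = 90 min (target ≥90)
- 5 × 25 = 125 min (target ≥120)
- 5 × 30 = 150 min (target ≥150)

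Every schedule meets its target. The ladder ends at the same 150 min that Table 3 uses as the cutoff for light-to-moderate activity.

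**2. The boundary.** Table 3 scores the point at ≤150 min, and 150 ≤ 150 is true. A participant who does exactly the last schedule at light-to-moderate intensity keeps the point. Clearing it needs more than 150 min (which the ≥150 target allows), more than 75 min of vigorous activity (Table 2 includes running and rope skipping), or other activity on top. This reads the item as cleared by satisfying any one of its three conditions; read literally, the word *or* would make it harder to clear.

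**3. Score arithmetic, with the other four items unchanged.**
- 3 points including activity: 3 − 1 = 2, frail becomes pre-frail.
- 4 points: 4 − 1 = 3, still frail.
- 5 points: 5 − 1 = 4, still frail.

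Reclassification from activity alone therefore happens only at exactly 3 points including activity. The score itself falls by one point for everyone who clears the item.

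**4. Size, by assumption.** Let *s* be the share of all participants at exactly 3 including activity, and *c* the difference between arms in the proportion of these who clear the item. The artefact in the share scoring 3 or more is *s* × *c*. The documents give neither input.
- Low case: *s* = 0.20, clearance 0.50 against 0.20: 0.20 × 0.30 = 0.06, or 6 points.
- High case: *s* = 0.50, clearance 0.75 against 0.10: 0.50 × 0.65 = 0.325, or about 33 points.

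**5. A second illustration, also assumed.** Suppose everyone is insufficiently active at baseline and the other four items are independent, each positive with probability *q* between 0.3 and 0.7. The share at exactly 3 including activity is then 6*q*²(1 − *q*)²: 0.265 at *q* = 0.3 or 0.7, and 0.375 at *q* = 0.5.
- Net clearance 50%: 0.5 × 0.265 = 0.13 to 0.5 × 0.375 = 0.19. A simple two-proportion comparison at 50 per arm gives P < 0.05 in 31–50% of trials.
- Net clearance 70%: 0.7 × 0.265 = 0.19 to 0.7 × 0.375 = 0.26, with P < 0.05 in 57–76% of trials.
- Mean score: net clearance of 50% shifts the mean by 0.5 points. With an assumed SD of 0.8–1.2, a two-sample comparison at 50 per arm gives P < 0.05 in 55–88% of trials.

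These chances come from simple two-group tests, not from the planned GEE. They show only that the artefact need not be small.

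**The case against.** The activity item belongs to the cited phenotype, and dropping it yields a non-standard score. The stated aim is the effect on health profile; delaying or reversing frailty is an expectation in the Conclusion, and no sentence says it will be judged on this score. Component analyses of a secondary outcome are commonly left to a full protocol or SAP. All of this is fair, and neither the choice of instrument nor the lack of a supplementary analysis is a fault in itself. What stands is that the article fixes the composition of the score, its cutoff and the comparison at 3 or more, in a trial whose treatment is one of the components.

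Several stronger readings are tempting but unsupported:
- **That the trial could not separate uptake from benefit.** TUG and device-measured walking speed, variability and symmetry are separate outcomes, and the component data are collected at each visit. A fall in frailty score with no change in TUG or gait would be visible.
- **That low activity is counted twice.** Table 3 has a distinct IPAQ category of low activity with its own criteria. The low activity in Other Secondary Outcomes is most naturally that category.
- **That completing the schedule clears the item.** Exactly 150 min of light-to-moderate activity does not.
- **That both visits are affected alike.** The intervention ends at 12 weeks, and Study Design says group 2 will be given the same guidance after the intervention. Activity at 24 weeks is not simply assigned exposure.
- **That the Fried activity item is certainly self-reported.** Table 3 names no instrument for it. Self-report is inferred from the use of the IPAQ and from the limitation in the Discussion.

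**Conclusion.** The point holds as a matter of interpretation for one secondary outcome, most directly at 12 weeks. The mechanism is in the text: uptake of the assigned activity can lower the frailty score by one point and can reclassify a participant who stands at exactly 3 including activity.

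The size is not known. The ranges of 6–33 and 13–26 percentage points rest wholly on assumed shares and clearing rates, and the 33 combines the most favourable value of every input. Entry is by the FRAIL scale, so even the baseline distribution of the Fried score is not given. The boundary at 150 min may reduce the effect. The primary outcome and the device gait outcomes are unaffected. A reader might infer that any frailty finding would be spurious, or that no frailty claim is possible without a difference on a four-item score; the documents support neither.

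**What to change.** Keep the five-item score and the share scoring 3 or more. Beside them, prespecify:
- the same GEE comparison on the four items other than activity (walking speed, grip strength, weight loss, fatigue; score 0–4);
- each of the five components reported by arm at 12 and 24 weeks;
- a sentence stating that the activity item is interpreted as uptake of the intervention, and that frailty will not be described as delayed or reversed on the five-item score alone if the four-item score shows no difference.

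The top target in Table 1 (≥150) and the cutoff in Table 3 (≤150) meet at the same value and must be reconciled, so that it is clear how a participant at exactly 150 min is scored.

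The cost is one derived variable from data already collected and a few sentences. The downside is that the four-item score is not the standard phenotype, is less comparable with other studies, and may show a smaller effect.
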